## Abstract

**Background:**

Adolescent depression can place a young person at high risk of recurrence and a range of psychosocial and vocational impairments in adult life, highlighting the importance of early recognition and prevention. Parents/carers are well placed to notice changes in their child’s emotional wellbeing which may indicate risk, and there is increasing evidence that modifiable factors exist within the family system that may help reduce the risk of depression and anxiety in an adolescent. A randomised controlled trial (RCT) of the online personalised ‘Partners in Parenting’ programme developed in Australia, focused on improving parenting skills, knowledge and awareness, showed that it helped reduce depressive symptoms in adolescents who had elevated symptom levels at baseline. We have adapted this programme and will conduct an RCT in a UK setting.

**Methods:**

In total, 433 family dyads (parents/carers and children aged 11–15) will be recruited through schools, social media and parenting/family groups in the UK. Following completion of screening measures of their adolescent’s depressive symptoms, parents/carers of those with elevated scores will be randomised to receive either the online personalised parenting programme *or* a series of online factsheets about adolescent development and wellbeing. The primary objective will be to test whether the personalised parenting intervention reduces depressive symptoms in adolescents deemed at high risk, using the parent-reported Short Mood & Feelings Questionnaire. Follow-up assessments will be undertaken at 6 and 15 months and a process evaluation will examine context, implementation and impact of the intervention. An economic evaluation will also be incorporated with cost-effectiveness of the parenting intervention expressed in terms of incremental cost per quality-adjusted life year gained.

**Discussion:**

Half of mental health problems emerge before mid-adolescence and approximately three-quarters by mid-20s, highlighting the need for effective preventative strategies. However, few early interventions are family focused and delivered online. We aim to conduct a National Institute for Health and Care Research (NIHR) funded RCT of the online personalised ‘Partners in Parenting’ programme, proven effective in Australia, targeting adolescents at risk of depression to evaluate its effectiveness, cost-effectiveness and usability in a UK setting.

**Trial registration {2a}:**

ISRCTN63358736. Registered 18 September 2019.

**Supplementary Information:**

The online version contains supplementary material available at 10.1186/s13063-022-06563-8.

## Administrative information

Note: the numbers in curly brackets in this protocol refer to SPIRIT checklist item numbers. The order of the items has been modified to group similar items (see http://www.equator-network.org/reporting-guidelines/spirit-2013-statement-defining-standard-protocol-items-for-clinical-trials/.)

### Background {6a}

Approximately half of lifetime mental disorders emerge before mid-adolescence and three-quarters by mid-20s [1]. Annual mental health treatment costs in the UK are estimated to increase to over £10 billion by 2026, with costs highest in the young [2]. Depression in adolescence is of particular concern [3]; approximately one in seven (14.4%) young people aged 11–16 have a mental health disorder, with almost one in ten experiencing an emotional disorder [4].

Adolescent depression and anxiety puts young people at risk of developing more severe affective disorders [4, 5], long-term psychosocial and vocational impairments, and increased risk of suicide [6, 7] as they mature, even when symptoms are sub-threshold [8]. Early identification and indicated interventions for those with low-level symptoms have been associated with positive outcomes; with meta-analyses showing a typical reduction in depression incidence of around 20% in the 3–24 months post-intervention [9, 10].

The development and implementation of preventative strategies for adolescents is a global priority [11]. In the UK, a government green paper and associated policy documents [12] highlight adolescence as a ‘critical period’ during which preventative strategies may be at their most effective.

Robust evidence delineating risk and protective factors associated with the development of adolescent depression and anxiety [13] provides a solid foundation for public health initiatives. Focusing on these potentially malleable psychosocial factors may improve outcomes for adolescents [14]. Strategic settings for initiatives have included schools, digital/print media and the internet but interventions are typically structured, face-to-face psychological therapies, predominantly targeted towards the adolescent themselves. Whilst such initiatives have demonstrated continued efficacy at 12 months post-intervention [15], they rarely include a family component [14, 16]. A recent meta-analysis has suggested, however, that explicitly targeting parents/carers of children aged 0–18 years can produce lasting benefits for internalising outcomes, with long-term effects on anxiety (up to 11 years post intervention) and depression (up to 5.5 years). Pooled effects suggested numbers-needed-to-treat (NNT) of 10 and 11 for preventing anxiety and depression respectively [17], figures similar to interventions directly targeting adolescents (NNT=11 [15];).

The present trial, therefore, focuses on the family setting, mindful of the need to empower parents/carers and equip them with a range of skills and knowledge with which to support their child’s emotional wellbeing. The close proximity of the family unit means that parents/carers are ideally placed to notice changes in their child’s emotional wellbeing and likely to have primary responsibility for initiating help-seeking and providing support [18]. However, a national survey of Australian parents revealed their knowledge about practical ways to help reduce their child’s risk of depression is less than optimal [19], and whilst intrinsically motivated to take action for their child’s wellbeing, this lack of awareness and skills may reduce their capacity to do so [20].

Despite global mental health policies and action plans prioritising preventative youth mental health strategies [12, 21, 22], there remains a gap in the provision of *evidence-based family resources* to upskill and improve knowledge and awareness of the risk and protective factors under parents’/carers’ direct control and influence [23]. Protective factors can be as fundamental as encouraging healthy sleep, diet and engaging in physical activity [24]. However, there is a strong evidence base for three key parental protective factors (*warmth*, *autonomy granting* and *monitoring*) and three risk factors (*inter-parental conflict*, *over-involvement* and *aversiveness* [25]). Such factors are akin to the concept of expressed emotion, wherein familial emotional climate and dialogical styles have been associated with psychosis relapse [26], poor behavioural and social outcomes for adolescents [27]. Most evidence-based targeted parenting interventions, however, are face-to-face, group programmes delivered by trained professionals. This can make them expensive and susceptible to a host of engagement barriers such as scheduling and privacy concerns, thereby limiting their public health benefit [28, 29]. Furthermore, whilst group programmes may offer social support [30], many families may prefer a private space to explore personal issues [17].

Digital technology offers such confidentiality and may be viewed as less stigmatising [28], more flexible and accessible [31]. Web-based programmes also offer greater potential for personalisation, screening individuals across a range of empirically derived risk and protective factors to target in an intervention [20], thereby ensuring thorough coverage of significant areas of importance and breadth without imposing unnecessary burden by the addition of less personally relevant topics [20], enhancing perceived relevance [32], effectiveness [33], scalability and sustainability [32]. Such tailored online programmes are viewed favourably by parents/carers [34], with positive effects observed in terms of relationships and behaviour [35].

Online personalised parenting programmes, therefore, may be a more efficacious and economically viable public health approach to prevention [36]. Yet few researchers are fully embracing digital tools for this purpose [37]. Indeed, a recent systematic review identified only one tailored web-based parenting intervention to prevent depression and anxiety disorders in adolescents—‘Partners in Parenting’ [20, 38]. The Australian programme targets up to nine modifiable parental domains, established through systematic review and meta-analysis of modifiable parenting factors associated with adolescent depression and anxiety [24] and the consensus of international experts [25]. A randomised controlled trial (RCT) of this programme, with 359 Australian parent-adolescent dyads, found greater improvement in desired parenting techniques in the personalised programme group at post-intervention, compared to an active control (Cohen’s *d*=0.51). Among adolescents with elevated depressive symptoms at baseline (*n*=105), the personalised programme group showed greater depression symptom reduction [39].

We have adapted the Australian online ‘Partners in Parenting’ programme for use in a UK setting and will conduct an RCT to test its effectiveness, cost-effectiveness and usability—‘An online *P*arenting *I*ntervention to *P*revent affective disorders in high-risk *A*dolescents: The PIPA Trial’.

### Objectives {7}

#### Primary objective

To test the effect of an online personalised parenting programme (relative to an active control) on severity of depressive symptoms in adolescents at high risk of developing affective disorders in the UK.

#### Secondary objectives

To test the effect of an online personalised parenting programme (relative to active control) on parenting behaviour, self-efficacy and mental wellbeing in parents/carers.To test the effect of an online personalised parenting programme (relative to active control) on emotional regulation, anxiety symptoms, emotional and behavioural difficulties and quality of life in adolescents.To evaluate the cost-effectiveness of an online personalised parenting programme.

### Trial design {8}

The PIPA trial is a two-arm, superiority, intention to treat RCT (allocation ratio 1:1). Parents/carers will be randomised to either the personalised parenting programme (intervention) or standard educational package (active control). Both will be delivered online and *not* by researchers. There will be three measurement time-points: baseline, 6 months post-randomisation and 15 months post-randomisation.

The research design includes a health economic evaluation to establish cost-effectiveness. A process evaluation will also explore participant experience to determine acceptability and usability of the programme by conducting a series of focus groups with parents/carers and teachers and in-depth interviews with family dyads (parents/carers and adolescents). A flow diagram of the trial is shown in Fig. 1.

**Fig. 1 Fig1:**
[figure not shown]
Trial flow diagram

## Methods

### Study setting {9}

The mid-year 2020 population of the UK was estimated to be 67.1 million, with around 6% (4 million) aged 11–15years [40]. Participants will be recruited through secondary schools in the UK. There are 4190 secondary schools in the UK and 4.1 million secondary school pupils [41].

Participants will also be recruited directly via social media (e.g. Facebook and Twitter) and parenting/family and other community groups in the UK. In January 2021, there were an estimated 53 million active social media users in the UK with an average of 1 h and 49 min spent using social media daily [42].

### Eligibility criteria {10}

Participants will confirm eligibility for the trial, with some data checks conducted by the trial team. Inclusion and exclusion criteria are detailed in Table 1.

**Table 1 Tab1:** Inclusion and exclusion criteria

	Parent/carer	Young person
**Inclusion criteria**	• Age ≥18 years • Biological parent/carer/non-biological parent/grandparent/legal guardian • Access to the internet and personal email account • Mobile phone number	• Aged 11–15 years • Parent/carer has given informed consent • Has a reading age of 11+ years • Access to mobile phone and internet • Living with participating parent/carer • Score 7 or above on Short Mood and Feelings Questionnaire (SMFQ)
**Exclusion criteria**	• Unable to access the PIPA database and/or Partners in Parenting website • Previous failed screening or randomisation in present trial • Participation in another parenting intervention in last 90 days	

### Who will take informed consent {26a}

Parents/carers will provide electronic consent for their own *and* their child’s participation via the PIPA trial website. Adolescents will be sent a text to confirm assent. Consent/assent forms will be held electronically at Warwick Clinical Trials Unit (WCTU), following WCTU Data Management and Security Standard Operating Procedures (SOPs).

### Additional consent provisions for collection and use of participant data and biological specimens {26b}

Consent/assent procedure includes the option for participants to permit any information collected to be used or shared anonymously with other researchers and to support future research.

## Intervention

### Explanation for the choice of comparators {6b}

The active control consists of five factsheets providing information to parents/carers about adolescent development representative of UK health promotion resources. We have chosen an active control in order to engage parents and aid retention for the duration of the trial.

### Intervention description {11a}

#### Personalised programme

The personalised programme is delivered online via the ‘Partners in Parenting’ website [20]. The programme fulfills the principles of the evidence-based Persuasive Systems Design model, which uses technology to influence behaviour change [43]. Principles include tailoring, feedback, personalisation and self-monitoring, all associated with greater programme adherence [44]. Adaptations for a UK context were made following feedback from a series of adaptation focus groups with parents/carers, teachers and adolescents.

After assessment of current parenting practices using the ‘Parenting to Reduce Adolescent Depression and Anxiety Scale’ (PRADAS [45]) and the ‘Parental Self-Efficacy Scale’ (PSES [46]) parents/carers will receive individually tailored feedback and will be recommended up to nine modules (targeting the nine modifiable parenting domains) (see Fig. 2).

**Fig. 2 Fig2:**
[figure not shown]
Logic model

Participants may accept recommended modules *or* select their own, with one module released per week until all selected have been released. Modules offer a range of parenting tips and information on adolescent mental health and wellbeing using illustrations, video and audio clips, vignettes, goal-setting exercises and ‘end-of-module’ quizzes (with immediate feedback to consolidate learning).

#### Standard educational package

The active control is also delivered via the ‘Partners in Parenting’ website and consists of five factsheets (to match expected mean number of modules received by the intervention group; *n* = 5.2 [39]) *without* tailored, actionable strategies for parents/carers and released in a set order on a weekly basis. Factsheets were adapted from highly credible resources in Australia (Raising Children [47], as used by the Australian RCT. They were modified for a UK context following feedback from adaptation focus groups with parents/carers and teachers. Factsheets cover the following topics: (1) Teen development, (2) The teenager’s developing brain, (3) The teenager’s changing body, (4) Resilience, and (5) Happy teenagers and teenage wellbeing.

### Criteria for discontinuing or modifying allocated interventions {11b}

The Participant Information Leaflet states that neither participants nor the research team will be able to choose or influence group allocation.

Parents/carers and adolescents may withdraw from the trial and/or interventions at any time without prejudice, with the option to volunteer a reason for withdrawal. Complete withdrawal will also withdraw the corresponding family member, who will be notified of this. Unless consent is *explicitly* withdrawn, participants will be followed up and data collected as per protocol until the end of the trial. Withdrawal forms will be completed by the PIPA trial team. All data up to the point of withdrawal will be retained unless requested otherwise.

### Strategies to improve adherence to interventions {11c}

Every 7 days after the intervention start date, an automated email will invite parents/carers in both groups to access their next module/factsheet, until all have been released. All participants will receive fortnightly check-in calls from research staff, following entry into the trial, alternated with text messages. These check-in calls will *not* deliver parenting advice but will be used to maintain engagement, address basic trial-related questions, encourage progression and enhance adherence.

### Relevant concomitant care permitted or prohibited during the trial {11d}

Participation in another parenting intervention will exclude individuals from participating in the current trial.

### Provisions for post-trial care {30}

A list of helpful resources will be available on the PIPA Trial website, should families require further support regarding mental health and wellbeing.

### Outcomes {12}

#### Primary outcome

A change in parent/carer-reported adolescent depression score between entry to trial and 15 months post-randomisation (Short Mood & Feelings Questionnaire – Parent reported; SMFQ-PR [48]).

### Participant timeline {13}

A timeline of assessments for participants is shown in Table 2. All assessments will be completed via the PIPA database.

**Table 2 Tab2:** Assessments and timeline for participants

Time-point	Baseline		6 months (post-randomisation)		15 months (approx. 12 months post-randomisation)	
	Parent/Carer	Young Person	Parent/Carer	Young Person	Parent/Carer	Young Person
**Pre-entry into trial**						
Participant details	**✓**					
Inclusion/exclusion criteria	**✓**					
Informed consent	**✓**					
Assent		**✓**				
Screening^a^		**✓**^a^				
**Trial**						
Medical history	**✓**					
SMFQ (primary outcome)^a^	**✓**	**✓**^a^	**✓**	**✓**	**✓**	**✓**
PRADAS	**✓**		**✓**		**✓**	
IPPA	**✓**	**✓**	**✓**	**✓**	**✓**	**✓**
PSES	**✓**		**✓**		**✓**	
DERS-SF		**✓**		**✓**		**✓**
Short WEMWBS	**✓**		**✓**		**✓**	
CAS-8		**✓**		**✓**		**✓**
SDQ	**✓**	**✓**	**✓**	**✓**	**✓**	**✓**
DAWBA		**✓**				**✓**
CHU-9D		**✓**		**✓**		**✓**
EQ-5D-5L-Y		**✓**		**✓**		**✓**
EQ-5D-5L	**✓**		**✓**		**✓**	
EQ5D-5L-Y proxy	**✓**		**✓**		**✓**	
Client service receipt inventory	**✓**		**✓**		**✓**	
Intervention satisfaction survey			**✓**		**✓**	

^a^SMFQ at baseline will be collected during screening for young person

#### Adolescents

Following assent, adolescents will complete the SMFQ [48].

#### Parents/carers

SMFQ data from a large population samples suggest that more than 20% of adolescents will report depressive symptoms [60]. Parents/carers of adolescents scoring ≥7 (indicative of elevated risk of depression and/or depressive disorder [61, 62]) will receive an automated message confirming eligibility. Families of those scoring <7 will be deemed ineligible and receive an automatically generated email or text informing them of this. Should they require further information or guidance, they will be directed to the list of helpful resources available on the PIPA trial website.

Whilst multiple parents/carers from the same family may participate in the programme, only one will be asked to complete baseline and follow-up measures. Baseline assessment of parenting practices (using PRADAS and PSES) will assess the nine modifiable parenting domains (see Fig. 2). Participants will then be randomly allocated to receive either the personalised programme or standard educational package.

### Sample size {14}

In the Australian RCT [39], a reduction in depressive symptoms (from pre- to post-intervention) in the subsample of adolescents (*n*=105) with elevated baseline depressive symptoms was greater in the intervention group compared to the active control (effect size 0.35; Cohen’s *d*, *n*=105). Assuming the correlation between pre- and post-intervention SMFQ scores is 0.5, 346 families would provide 90% power to detect a difference of 0.35 in the primary outcome between trial arms at the 5% level. To allow 20% loss to follow-up, the total family recruitment target is 433, enabling sufficient numbers for sub-group analyses (for example, young people from low socioeconomic status and/or BME backgrounds).

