### Methods for additional analyses {20b}

#### Sub-group and adjusted analyses

Separate analysis of primary outcome and effect estimates will be conducted for school location (proxy for social deprivation), parents’/carers’ highest educational level (surrogate for socioeconomic status) and ethnicity. All analyses will be adjusted by design variables (school, age group, gender of young person, gender of parent/carer and total number of parents accessing modules/factsheets).

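### The recruitment target of 433 covers only the overall comparison and 20% attrition, so the statement that it gives enough families for subgroup analyses has no support, and separate subgroup analyses need an interaction to interpret them

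*Protocol article*

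**What the plan says.** Section Sample size {14} of the protocol article sizes the trial on the overall comparison: "346 families would provide 90% power to detect a difference of 0.35 in the primary outcome between trial arms". The effect comes from the subsample with elevated symptoms in the Australian trial ("effect size 0.35; Cohen’s *d*, *n*=105"), and the pre-post correlation is taken as 0.5. Attrition is then added: "To allow 20% loss to follow-up, the total family recruitment target is 433". The same sentence goes on to describe that target as "enabling sufficient numbers for sub-group analyses (for example, young people from low socioeconomic status and/or BME backgrounds". No subgroup share, subgroup effect, precision or subgroup power is given.

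The section Sub-group and adjusted analyses, under Methods for additional analyses {20b}, sets out the approach: "Separate analysis of primary outcome and effect estimates will be conducted for school location", with parental education and ethnicity as the other two factors. It names no arm-by-subgroup interaction and does not describe these analyses as exploratory.

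**The concern.** The adequacy phrase sits inside the power justification, directly after a 90% power figure. A reader will naturally take it to mean that the design was sized with the named groups in mind. If it was not, a null result in low-income or minority-ethnic families could be taken as an informative negative when it mainly reflects small numbers.

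The stated method adds to this. An estimate made separately in each stratum does not answer whether the effect differs between strata. Where one stratum is much smaller than the other, one result can be significant and the other not, even though the effect is the same in both. For a programme meant to inform public-health policy, a conclusion that it works only in some communities would matter, and it should not rest on a difference in sample size.

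**Working it through.** **Inputs from the protocol article.** Effect 0.35 (Cohen's d), power 90%, 5% level, pre-post correlation 0.5, 346 families, 20% loss and target 433 (all from Sample size {14}); 1:1 allocation (Trial design {8}). The article does not say whether the test is one- or two-sided. Two-sided is assumed, and it reproduces the stated number.

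**Step 1: the plan's own figures.** With correlation 0.5, the SD of the change score is √(2(1 − 0.5)) = 1 baseline SD, so d = 0.35 applies unchanged. A two-sample t-test at 90% power needs 172.5 families per arm, rounded up to 173, or 346 in total. This matches exactly. Attrition: 346/0.8 = 432.5, rounded up to 433. This also matches exactly. Conversely, 433 × 0.8 = 346.4, so the expected number analysed is the 346 needed for the overall comparison, with no families to spare.

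**Step 2: power within a subgroup.** The article gives no subgroup shares, so those below are assumptions. For a subgroup of n families split equally between arms, the t-test noncentrality is 0.35 × √(n/4). The calculation uses 346 analysed and a true effect of 0.35 in everyone.

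| Assumed share | n in subgroup | Power in subgroup | Power in the rest |
|---|---|---|---|
| 50% | 173 | 63% | 63% |
| 30% | 104 | 42% | 77% |
| 20% | 69 | 30% | 83% |
| 10% | 35 | 17% | 87% |

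**Step 3: power for a difference between subgroups.** The standard error of the interaction is √(4/n₁ + 4/n₂).

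- 173/173: √(4/173 + 4/173) = 0.215. Power for an interaction of 0.35 is Φ(0.35/0.215 − 1.96) = 37%.
- 69/277: √(4/69 + 4/277) = 0.269. Power is Φ(0.35/0.269 − 1.96) = 26%.
- The smallest interaction detectable with 80% power is 2.80 × SE: 0.60 SD (50/50) or 0.75 SD (20/80), about twice the planned overall effect.

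**Step 4: discordance under a uniform effect.** If the strata are tested separately, with powers p₁ and p₂, the chance that exactly one is significant is p₁(1 − p₂) + p₂(1 − p₁).

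- 50/50: 2 × 0.629 × 0.371 = 47%.
- 20/80: 0.299 × 0.173 + 0.827 × 0.701 = 63%.

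These are probabilities per factor, and three factors are planned.

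**Step 5: sensitivity to baseline adjustment.** If adjustment for baseline reduced the SD to √(1 − 0.5²) = 0.866, power within a subgroup would be about 76% (half the sample) or 39% (one fifth), by normal approximation. Interaction power would be 47% or 32%. The conclusion does not change.

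**The case against.** The strongest reply has three parts.

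First, the article attaches 90% power only to the overall difference. Its subgroup clause gives no power, effect or test, and could mean no more than enough families to produce subgroup estimates. That reading is possible. But the clause stands within the sample size justification as a consequence of the target, and nothing in the article marks it as descriptive. If estimation is all that is meant, the text should say so.

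Second, a reader might infer that the plan commits to comparing significance across strata, that it rejects an interaction test, or that separate analyses are bound to produce false subgroup differences. The documents support none of these. The subgroup section promises effect estimates by factor. It states no stratum-wise decision rule and does not exclude an interaction. One may well be specified in a statistical analysis plan that is not shown, so its absence from a condensed article is no fault in itself. Discordant significance misleads only if someone compares it across strata, and it is likely rather than certain. This part of the objection stands and limits the point about method to a clarification.

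Third, the subgroup shares are assumed, and education and ethnicity may have more than two levels. That is correct: the figures illustrate the size of the problem and do not predict this trial's results. In the two-stratum calculation, however, even the most favourable case for the smaller group, an equal split, gives 63% against the trial's own 90%. An unseen analysis plan cannot supply families that the sample size calculation did not include.

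**Conclusion.** The point holds in two parts of unequal strength. The firm part is that the adequacy phrase in the sample size section is unsupported, because the target is the overall-effect sample inflated for attrition and nothing more. This follows from the article's own numbers and needs no assumption about subgroup shares.

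The second part is conditional. Separate analysis is the only subgroup method stated, and it invites a comparison of significance that would often mislead: about 47% to 63% per factor under a uniform effect of 0.35, 346 families analysed, and assumed splits of 50/50 to 20/80. The primary analysis, the sample size for it and the main conclusion of the trial are unaffected. The change should be made, because the article states a design property that the trial does not have.

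**What to change.** In Sample size {14}, delete the phrase on sufficient numbers for subgroups. State instead that the sample is powered for the overall effect only and that subgroup analyses are exploratory.

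In Sub-group and adjusted analyses, state that differences between subgroups will be judged by an arm-by-subgroup interaction, fitted for each factor in one model on all families. Report the interaction estimate with its 95% confidence interval, and derive the stratum effects and their intervals from that same model. If the statistical analysis plan already says this, the article need only be brought into line with it.

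The cost is wording and a less favourable stated claim. No extra families or data are needed.
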